### Statistical analysis

The statistical analysis will be performed by two independent statisticians. The statisticians are blinded to treatments and study protocol. Statistical analysis will be conducted on the basis of an intention-to-treat (ITT) analysis. Missing values will be imputed by the last observation carried forward (LOCF) method. Categorical data will be analyzed with the McNemar chi-square test. Continuous data will be analyzed by analysis of variance (ANOVA). If the data trend over time and over time by treatment interactions, the repeated-measures ANOVA will be used. A *P* value less than 0.05 is regarded as statistically significant.

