### Outcomes

The primary outcomes of the study include patients’ response to the treatment [13]. The secondary outcomes include dyspeptic symptoms [14], quality of life [15], mental status [16, 17], fasting serum gastrin, motilin, and ghrelin concentrations, and adverse events. Each outcome variable will be assessed before and after treatment, and follow-up will be conducted at 4, 8, and 12 weeks in all groups (Fig. 3).

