#### Secondary outcomes

Dyspeptic symptoms will be assessed by the Chinese version of the Nepean Dyspepsia Index (NDI) [14], including the intensity, frequency, and level of interference of postprandial fullness, early satiety, epigastric pain, and epigastric burning sensation. The intensity of each symptom is graded and scored as follows: 0, absent; 1, mild; 2, moderate; 3, severe; 4, critical. The frequency of each symptom is also graded: 0, absent; 1, occasionally (1–2 days/week); 2, sometimes (3–5 days/week); 3, frequently (every day, but intermittent symptoms); 4, continuous symptoms. The level of interference of each symptom is scored and graded as follows: 0, none; 1, mild interference; 2, moderate interference; 3, severe interference; 4, critical interference. The number in front of each grading indicates the score of the corresponding symptom; the score for each symptom in the checklist of cardinal dyspeptic symptoms is calculated by adding its scores in the corresponding frequency, severity, and level of discomfort. The dyspeptic symptom sum score (DSSS) is the sum score of the four symptoms in the checklist.

The quality of life will be evaluated by the Short-Form 36 questionnaire (SF-36) [15]. Mental status will be measured by the Zung Self-Rating Depression Scale (SDS) [16] and Self-Rating Anxiety Scale (SAS) [17]. The SF-36 measures quality of life (QoL) across eight domains; the score of each domain = [(actual raw score − lowest possible raw score)/raw score range] × 100. For the SDS score, the following equation is used: SDS Index = Raw Score × 1.25. The grading of the SDS is as follows: SDS Index less than 53 points is considered normal, 53–62 is considered mild depression, 63–72 as moderate depression, and 73 and higher as severe depression. For SAS grading, the following categories are used: normal range (less than 50), mild anxiety (50 to 59), moderate anxiety (60 to 69), and severe anxiety (70 and higher).

Fasting serum levels of gastrin, motilin, and ghrelin will be measured by the enzyme-linked immunosorbent assay. A fasting venous blood sample will be drawn from the basilic vein prior to breakfast early in the morning before and after treatment.

Any adverse reactions of patients will be recorded in the case report form (CRF), including swelling, pain, bruise at the sites of needle insertion, or discomfort, palpitation, dizziness, etc., after acupuncture.

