### Sample size

The sample size calculation is based on the results of trials by Li et al. [18] and Ji et al. [19] and the recommendation of acupuncture specialists in China. The mean value of the NDI score in the 2.5 Hz group is 82.28, the standard deviation is 6.97; the mean value of the NDI score in the 2 Hz group is 86.73, the standard deviation is 7.10; the mean value of the NDI score in the 1 Hz group is 76.50, the standard deviation is 8.06; the mean value of the NDI score in the control group is 65.85, the standard deviation is 16.47. To detect a significant difference between any two groups with a power of 90% and a type I error of 5%, the calculated number of patients is 17. Considering a 30% dropout rate, the total sample size required is 88 patients.

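### For the continuous secondary outcomes, the plan leaves out the baseline value it collects and lets the observed data decide whether ANOVA or repeated-measures ANOVA is used

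*Protocol article*

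**What the plan says.** The Statistical analysis section of the protocol article gives two sentences on continuous data. The first is "Continuous data will be analyzed by analysis of variance (ANOVA". The second is "If the data trend over time and over time by treatment interactions, the repeated-measures ANOVA will be used". Neither mentions a baseline covariate, says whether the outcome is a final or a change score, or names the visit at which plain ANOVA is applied. The same section imputes missing values by last observation carried forward (LOCF) and says that a P "value less than 0.05 is regarded as statistically significant".

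A baseline value exists. The Outcomes section says "Each outcome variable will be assessed before and after treatment" and that "follow-up will be conducted at 4, 8, and 12 weeks in all groups", which makes five time points. For serum gastrin, motilin and ghrelin, the Secondary outcomes section describes fasting samples taken "early in the morning before and after treatment".

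The continuous outcomes are the dyspeptic symptom sum score (DSSS), the SF-36 domains, the depression and anxiety scales, and the three hormones. All are secondary. The primary outcome is a binary response rate, which this point does not touch.

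**The concern.** There are two separate problems.

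The first is precision. With 88 patients allocated 1:1:1:1 there are 22 per arm, or 17 on the article's figure before the dropout allowance. In so small a trial, an adjustment that uses data already in hand should not be passed over.

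The second is error control. As written, the switch to repeated-measures ANOVA depends on what the data show. One of its two triggers, the time-by-treatment interaction, is itself a treatment effect. If a significant interaction leads to a repeated-measures claim, and a non-significant one leads to a further look with plain ANOVA, each outcome gets two chances to succeed at the 5% level. Even where the error rate holds, the rule leaves two candidate analyses per outcome, with no visit fixed for one of them.

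**Working it through.** **The plan's own figure.** A one-way omnibus F test (noncentral F, alpha 0.05, power 0.90) on the four means in the Sample size section, with a common SD equal to the largest one stated (16.47), gives n = 17 per group with power 0.905. Then 17 × 1.3 = 22.1, taken as 22, and 22 × 4 = 88. Both stated figures are reproduced without any baseline adjustment.

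**Precision.** The correlation r between baseline and outcome is not in the article, so a range is assumed. With equal variances at the two times, and in units of the single-visit variance:

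- ANOVA of the post-treatment score: 1
- ANOVA of the change score: 2(1 − r)
- ANCOVA: 1 − r²
- ANCOVA relative to change score: (1 − r²) / [2(1 − r)] = (1 + r)/2

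| r (assumed) | ANCOVA v post score | Variance cut | ANCOVA v change score | Variance cut |
|---|---|---|---|---|
| 0.3 | 0.91 | 9% | 0.65 | 35% |
| 0.5 | 0.75 | 25% | 0.75 | 25% |
| 0.7 | 0.51 | 49% | 0.85 | 15% |

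In patients, 17 per arm under ANCOVA carry the information of 17/0.91 = 18.7, 17/0.75 = 22.7 or 17/0.51 = 33.3 per arm under post-score ANOVA. Against change-score ANOVA the figures are 17/0.65 = 26.2, 17/0.75 = 22.7 and 17/0.85 = 20.0.

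**Error rate of the conditional rule.** This was simulated under the null with 4 groups of 17, 5 time points and 20,000 runs per setting. Compound symmetry was assumed with correlation 0.3, 0.5 or 0.7, with no time trend or a common linear trend of 0.3 SD per visit. Plain ANOVA was taken at the end of treatment.

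| Reading of the rule | Type I error across settings |
|---|---|
| Plain ANOVA alone | 0.048–0.051 |
| Interaction test alone | 0.048–0.053 |
| Significant interaction is claimed; otherwise plain ANOVA | 0.092–0.096 |
| Time trend or interaction triggers the switch, and a group or interaction effect is claimed; otherwise plain ANOVA | 0.094–0.103 |
| Only the time trend triggers the switch, and the interaction alone is tested; otherwise plain ANOVA | 0.048–0.052 |

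As a check, two independent 5% tests would give 1 − 0.95² = 0.0975. The third and fourth rows lie close to that value, as two nearly separate chances would. The last row is not inflated: only one treatment test is carried out, and a trend common to all arms decides which.

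**The case against.** **A condensed article.** A journal article commonly leaves covariate lists to an analysis plan, and nothing here forbids adjustment. If repeated-measures ANOVA is used, baseline may enter as one of the time points. This has weight, and it is why baseline adjustment is put as an improvement to the stated method and not as an error. It does not answer the second problem, because the conditional rule is stated in the article itself.

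**Looser wording.** The second sentence might only mean that repeated-measures ANOVA serves questions about time. That is possible, but as written it is a condition on the data, and either reading calls for rewording.

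**Stronger readings that the article does not support.**

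- *Chance baseline imbalance invalidates the ANOVA.* It does not. Under randomisation the unadjusted analysis is unbiased on average and keeps its error rate; the loss is precision.
- *The error rate is certain to double.* It depends on the reading, as the last row of the second table shows.
- *Adjustment is worth 96% more patients.* That is 1/0.51, which holds only at r = 0.7 against post scores. Against change scores at the same r, 1/0.85 gives about 18%.
- *The planning SDs, 6.97 to 16.47, show that a pooled variance will distort the pairwise tests.* These SDs come from external trials. One belongs to a group that is not an arm of this trial ("The mean value of the NDI score in the 2.5 Hz group is 82.28, the standard deviation is 6.97"; the arms are 1, 2 and 3 Hz and control). Their means, 65.85 to 86.73, exceed the DSSS maximum of 4 symptoms × 3 items × 4 points = 48. They are not evidence about these outcomes as scored here. The article also specifies no pairwise contrast or error term.

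**Conclusion.** The point holds for the continuous secondary outcomes and should be corrected. It does not threaten the primary result.

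Omitting baseline gives up 9% to 49% of residual variance if post scores are meant, or 35% down to 15% if change scores are meant, for r from 0.3 to 0.7. These figures rest on an assumed r and on equal variances at the two times.

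The conditional choice of model raises the null error rate to about 9–10% when a significant interaction (or any repeated-measures treatment effect) counts as a finding and plain ANOVA is the fallback. It leaves the rate near 5% when only the overall time trend triggers the switch and the interaction alone is then tested. The article does not say which applies, and that gap is the defect. The simulated rates assume compound symmetry, 17 per arm and plain ANOVA at the end of treatment.

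**What to change.** For each continuous outcome, prespecify one model that is used whatever the data show, with the treatment contrast at a named visit, for example the end of treatment.

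- **Outcomes measured at several visits (DSSS, SF-36, depression and anxiety scales):** a mixed model for repeated measures with arm, visit, arm-by-visit and the baseline value. Use a covariance common to all arms, with a named simpler structure as fallback; separate covariances per arm would be too heavy for 17 to 22 patients per arm. State that this model replaces LOCF for these outcomes.
- **Serum hormones (one sample before and one after treatment):** ANCOVA of the post-treatment value on arm and baseline.
- **Pairwise contrasts:** heteroscedasticity-robust or Welch-type standard errors may be added as a precaution, without citing the planning SDs as the reason.

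Delete the sentence that makes repeated-measures ANOVA depend on the data. The cost is wording and routine programming; no new data are needed. The article reports recruitment as ongoing, so the change should be dated and made before unblinding.

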### Quality control and dropout criteria

All researchers will be required to undergo special training, including trial design, patient inclusion and exclusion criteria, and proper completion of the CRF. All practitioners, who have majored in acupuncture and received an acupuncture degree, are qualified doctors of traditional Chinese medicine. Patients who want to stop participating in this study, do not complete the treatment over two visits, violate the study protocol, withdraw consent for participation, or use prohibited treatments for FD will be dropped from the study. The reasons for dropouts and withdrawals from the study will be fully recorded.

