### Participants

#### Inclusion criteria

Participants will be included if they: (1) meet the Rome III FD criteria [1] (the new diagnostic standard for FD) and have clinical symptoms of epigastric pain syndrome (EPS); (2) are between the ages of 18 and 60 years; (3) have received no other treatments related to the gastrointestinal system 1 week before enrollment and during the study; (4) are willing to agree with the study protocol and sign a written informed consent.

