#### MA manipulation groups A, B, and C

The main acupoints ST36, PC6, and RN12 will be needled in each group. Additional acupoints will also be used based on symptom differentiation. For stagnation of liver qi, RN17 and LR13 (bilateral) are added; for deficiency of spleen qi and stomach qi, one adds BL20 (bilateral) and BL21 (bilateral); for stomach disorder due to liver qi, LR14 (bilateral) and LR3 (bilateral) are added; for damp heat in middle Jiao, one adds SP9 (bilateral) and ST44 (bilateral). Acupoints will be localized according to the 2008 World Health Organization standards [12]. Sterilized stainless steel needles (Φ0.25 mm × 25 mm or 0.25 mm × 40 mm, Tianjin Hua Hong Medical Co., Ltd., Tianjin, China) will be used for all acupuncture procedures. The length of the needle will be chosen according to the acupoint.

After a *de qi* sensation is achieved, the needles in MA manipulation groups A, B, and C will be respectively manipulated manually with three different frequencies (1, 2, or 3 Hz) of lifting-inserting MA manipulations (see Table 1). The lifting-inserting MA manipulation procedure is shown in Fig. 2. Briefly, after *de qi*, the lifting-inserting MA manipulation will be performed for 1 minute, three times, separated by 10-minute intervals. The entire procedure takes 33 minutes. The acupuncture treatment consists of 10 sessions over a period of 2 weeks (one session per day, five continual sessions per week, with a 2-day interval between the 2 weeks) after randomization. All participants will be followed up three times in 10 weeks after treatment (at 4, 8, and 12 weeks).

**Table 1 Tab1:** Parameters of three different lifting-inserting MA manipulations in MA manipulation groups

MA manipulation group	Frequency (Hz)	Operation of MA	Depth (mm)	Duration (s)
Group A	1	Neutral reinforcement and reduction	2–3	60
Group B	2			
Group C	3			

*MA* Manual acupuncture

In neutral reinforcement and reduction, the needle is perpendicular to the skin, and the force and amplitude of the lifting-inserting displacement is uniform; the lifting-inserting distance is 2–3 mm

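### The dropout rule removes non-adherent patients from the study, not only from treatment, so outcomes that the intention-to-treat analysis needs are not collected

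*Protocol article*

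**What the plan says.** The Statistical analysis section commits to the population in one sentence: "Statistical analysis will be conducted on the basis of an intention-to-treat (ITT) analysis". The next sentence deals with gaps: "Missing values will be imputed by the last observation carried forward (LOCF) method".

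The Quality control and dropout criteria section lists who leaves. Besides patients who want to stop, it names those who "do not complete the treatment over two visits" and those who "violate the study protocol, withdraw consent for participation, or use prohibited treatments for FD will be dropped from the study". For these patients it says only this: "The reasons for dropouts and withdrawals from the study will be fully recorded". It does not mention further outcome assessments.

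On timing, the intervention section says "The acupuncture treatment consists of 10 sessions over a period of 2 weeks", starting after randomisation. It also promises follow-up without exception: "All participants will be followed up three times in 10 weeks after treatment (at 4, 8, and 12 weeks"). The Primary outcomes section judges the IRR both at the end of treatment and at follow-up.

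The Inclusion criteria require that participants "have received no other treatments related to the gastrointestinal system 1 week before enrollment and during the study". The last part of that criterion cannot be known at enrolment.

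**The concern.** Intention-to-treat means that each randomised patient is followed and analysed in the allocated arm, whatever happens to adherence or other treatment. The dropout rule treats missed sessions, protocol violations and other dyspepsia treatment like withdrawal of consent: all of them end participation in the study. Withdrawal of consent is a legitimate reason to stop observing a patient. The other three call at most for a decision about treatment, and the outcome can still be measured.

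Two features make the loss matter. First, use of another dyspepsia treatment is plausibly linked to returning pain, so some of the lost outcomes may depend on response. If response or relapse differs by frequency, which is the trial's hypothesis, the loss can differ by arm. Second, violation of the protocol carries no severity threshold in this text, so the rule could reach many patients or few.

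An analysis plan can define analysis sets, but it cannot recover assessments that were never made. The Trial status section says that recruitment is ongoing.

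**Working it through.** **Inputs from the article.** Total 88 patients and a 30% dropout allowance (Sample size); allocation 1:1:1:1 (Recruitment, randomization, allocation concealment, and blinding); assessments before treatment, after treatment and at weeks 4, 8 and 12 (Outcomes).

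**The plan's own dropout figure.** The article states 17 patients without saying per what. Read as per group, 4 × 17 × 1.30 = 88.4, which gives the stated 88, or 88 / 4 = 22 per arm. The 30% corresponds to 0.30 × 88 = 26.4 patients, or 0.30 × 22 = 6.6 per arm. It is an all-cause allowance that includes voluntary stopping and withdrawal of consent. It does not estimate drops for missed treatment, violation or prohibited treatment, and no such rate is given.

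**What LOCF records for a dropped patient.** The IRR requires improvement by at least two scores or absence of symptoms. A carried-forward baseline shows no improvement, and a patient enrolled for epigastric symptoms is not symptom-free at baseline.

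| Time of drop | Value carried forward | Recorded at later assessments | Direction if wrong |
|---|---|---|---|
| During the 2-week course, before the post-treatment assessment | Baseline | Non-responder | IRR too low |
| During follow-up, responder at last assessment, then relapsed | Response | Responder | Follow-up IRR too high |
| During follow-up, non-responder at last assessment, would have improved later | Non-response | Non-responder | Follow-up IRR too low |

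Missed-session drops arise during the course and so fall mainly in the first row. Drops for prohibited treatment can occur at any time; those after response and relapse fall in the second row. The second row cannot affect the end-of-treatment IRR.

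**Size per misclassified patient.** Shift in one arm's IRR = k / 22, where k is the net number of patients misclassified in one direction. The values of k are assumptions.

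| k | Shift (percentage points) |
|---|---|
| 1 | 1/22 = 4.5 |
| 2 | 2/22 = 9.1 |
| 3 | 3/22 = 13.6 |
| 4 | 4/22 = 18.2 |

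For a comparison of two arms, the error is the difference between their shifts. Equal shifts in the same direction cancel. Two patients too many in one arm and two too few in another give 9.1 + 9.1 = 18.2 points.

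**The case against.** The strongest defence is that the two sections can be read together: a dropped patient has missing later visits, these are imputed, and the patient is analysed as randomised. This stands as far as the analysis set is concerned. A reader might infer that dropped patients are removed from the intention-to-treat population, so that the article flatly contradicts itself. No sentence says so, and intention-to-treat with LOCF can keep all 88 in the denominator. It does not answer the loss of data: those patients are then counted with values from before the event, although a real assessment could have been made.

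A reader might also infer that the rule inflates response rates, because all the listed events signal poor response. The article does not support that. Sessions can be missed and the protocol breached for reasons unrelated to pain, and a drop before the post-treatment assessment counts as non-response. Only the relapsed responder dropped during follow-up pushes the IRR up.

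The restriction on other gastrointestinal treatment during the study can fairly be read as a condition that patients accept at entry; nothing in that criterion orders exclusion after randomisation. It is also the article's only description of which other treatments are barred, so deleting it would remove a rule the trial needs.

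Finally, part of the harm comes from LOCF and not from the drop rule alone. That is true, and any separate comment on LOCF should not count it again. But the drop rule creates the gaps that LOCF fills.

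**Conclusion.** The point holds in a limited form. As written, the rule ends outcome collection for non-adherence, protocol violation and prohibited treatment. This weakens the intention-to-treat analysis and sits badly with the promise to follow all participants. Exclusion from the analysis set is not shown, nor is a single direction of bias.

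The size is conditional: about 4.5 points of IRR per misclassified patient, and about 4.5 to 18 points for an assumed 1 to 4 patients in an arm of 22. This rests on equal arms of 22, on LOCF being applied to the IRR as stated, and on the rule being applied literally. If no outcome is misclassified, the shift is zero.

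**What to change.** 1. In the dropout criteria, separate stopping study treatment from leaving the study. Which events should end treatment is for the protocol's authors to decide and is not touched here.
2. State that every randomised patient keeps the end-of-treatment and week 4, 8 and 12 assessments unless consent for follow-up is withdrawn.
3. State that all randomised patients are analysed as allocated, and that exclusions for adherence or violation apply only in a per-protocol sensitivity analysis.
4. Pre-specify one handling of prohibited dyspepsia treatment in the IRR. Counting it as non-response and using the observed outcome regardless are both defensible but answer different questions. Either way, the treatment and its date must be recorded.
5. Keep the restriction on other gastrointestinal treatment, but express its during-study part as a condition of participation and not as an eligibility criterion, so that a later breach is not a ground for exclusion from the analysis.

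The cost is a short amendment and some already scheduled follow-up visits for patients who would otherwise have been dropped. It should be made while recruitment continues, because assessments not made cannot be recovered.
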